## 4. SCHEDULE OF ACTIVITIES FOR STUDY 888MS002

**Table 1: Schedule of Activities**

| Assessments                                                                       | Baseline Visit                                                                            | Follow-Up Visit(s)  | Unscheduled Visit(s)  |
|-----------------------------------------------------------------------------------|-------------------------------------------------------------------------------------------------------|---------------------------------|-----------------------------------|
| Informed Consent/Assent Form(s)                                    | X                                                                                                     |                                 |                                   |
| Enrollment and Registration                                                       | X                                                                                                     |                                 |                                   |
| Sample Requisition Form                                               | X                                                                                                     | X                               | X                                 |
| Blood Collection for RNA, Serum, and Whole Blood Biomarker Samples  | X                                                                                                     | X                               | X                                 |
| Blood Collection for DNA Sample                                       | X                                                                                                     |                                 |                                   |
| SAE Reporting                                                                     | -----Only SAEs related to the venipunctures/blood draws will be collected during this sub-study.----- |                                 |                                   |

DNA = deoxyribonucleic acid; K2 EDTA = potassium ethylenediaminetetraacetic acid; MS PATHS = Multiple Sclerosis Partners Advancing Technology and Health Solutions; RNA = ribonucleic acid; SAE = serious adverse event.

 The Baseline Visit may occur concurrently with enrollment in Study 888MS001 or at any point thereafter prior to the end of that study.

 After the Baseline Visit, annual Follow-Up Visits will typically coincide with routine clinical visits for the duration of the study but not occur more frequently than 10 months since the last Baseline or Follow-Up Visit. Unscheduled visits may occur for clinical activity as defined in Section 7.2.3. After an Unscheduled Visit, the next annual Follow-Up Visit should occur no sooner than 10 months later.

 The Investigator will verify patient eligibility for study participation prior to signing of the informed consent (and assent, if applicable) form(s).

 Written informed consent must be obtained from any patient (or their legally authorized representative) who opts to participate in this biobanking sub-study; an additional written consent must be obtained from patients (or their legally authorized representatives) who elect to provide blood samples for genetic testing. Patients under 18 years of age who have the capacity should provide written assent in addition to the parental/guardian consent. The consent/assent form(s) must be signed and dated before any data collection is performed. Patients may withdraw consent/assent at any time, and no withdrawal visit is required.

 The sample requisition form will document the following information: date and time of sample collection, time of last meal, smoking status, and reason for unscheduled visit (if applicable).

 In patients ≥18 years of age, blood collection for future biomarker assessments will typically occur during routine clinical visits but not more frequently than every 10 months. Blood collection for these samples will total 28 mL whole blood: 5 mL into 2 PAXgene RNA tubes (2.5 mL each) for RNA, 17 mL into 2 SST™ tubes (8.5 mL each) for serum, and 6 mL into one 6-mL K2 EDTA tube for epigenetic and other whole blood biomarkers.

 In patients 8 to 17 years of age (inclusive), blood collection for future biomarker assessments will typically occur during routine clinical visits but not more frequently than every 10 months. Blood collection for these samples will total 13.5 mL whole blood: 5 mL into 2 PAXgene RNA tubes (2.5 mL each) for RNA and 8.5 mL into one 8.5-mL SST™ tube for serum.

CONFIDENTIAL

The information contained herein may not be used, disclosed, or published without the written consent of Biogen MA Inc.

In patients  $\geq 18$  years of age, blood collection for DNA samples will total 10 mL whole blood into one 10-mL K2 EDTA tube for genetic testing. In patients 8 to 17 years of age (inclusive), blood collection for DNA samples will total 6 mL whole blood into one 6-mL K2 EDTA tube for genetic testing. For all patients, collection of the genetic testing sample is preferred at the Baseline Visit but may be completed at any single visit during study participation. Note: All blood collection volumes may vary slightly across sites based on tubes available in different countries.

CONFIDENTIAL

The information contained herein may not be used, disclosed, or published without the written consent of Biogen MA Inc.

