#### **7.2.2. Follow-Up Visits**

After the Baseline Visit, annual Follow-Up Visits will typically coincide with routine clinical visits for the duration of the study but not occur more frequently than 10 months since the last Baseline or Follow-Up Visit.

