#### **7.2.3. Unscheduled Visits**

Unscheduled Visits will be permitted for the following events as determined by the Investigator:

1. Relapse
  - a. For the purposes of this study, relapses are defined as new or recurrent neurologic symptoms not associated with fever, lasting at least 24 hours. New or recurrent neurologic symptoms that evolve gradually over months are to be considered disease progression, not an acute

CONFIDENTIAL

The information contained herein may not be used, disclosed, or published without the written consent of  
Biogen MA Inc.

relapse. New or recurrent neurologic symptoms that occur fewer than 30 days following the onset of a relapse as defined above are to be considered part of the same relapse. An Unscheduled Visit for a relapse should occur within 30 days of the relapse onset.

2. MRI activity

- a. For the purposes of this study, MRI activity is any new or enlarging T2 lesion, gadolinium enhancing lesion, or brain atrophy. MRI activity can be based on any MRI (i.e., the MRI does not have to be from a Siemens 3T scanner using the MS PATHS 3D FLAIR and 3D MP-RAGE acquisition sequences). An Unscheduled Visit for MRI activity should occur within 30 days of the MRI acquisition.

3. MS PATHS MRI obtained

- a. For the purposes of this study, a MS PATHS MRI is an MRI acquired on a Siemens 3T scanner using the MS PATHS 3D FLAIR and 3D MP-RAGE acquisition sequences. An Unscheduled Visit for a new MS PATHS MRI should occur within 30 days of MRI acquisition.

4. Disease-modifying therapy (DMT) switch

- a. For the purposes of this study, a DMT switch is the initiation of a new therapy which has an approved indication in the United States or European Union for the treatment of MS or sub-type of MS. Therapies indicated solely for symptomatic treatment are excluded. An Unscheduled Visit for a DMT switch should occur within 30 days of the first administration of the new therapy.

5. Disease-modifying therapy (DMT) switch follow-up

- a. An Unscheduled Visit for a DMT switch follow-up should occur within 90-240 days after the first administration of the new DMT.

After an Unscheduled Visit, the next annual Follow-Up Visit should occur no sooner than 10 months later.

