## **11. STUDY PROCEDURES**

See Section 4 for the timing of all study procedures.

As part of this biobanking sub-study, patients will provide consent/assent, register for the study, and have blood drawn. In addition, the study staff will complete a sample requisition form (SRF) per Section 11.2.

Future biomarker and biologic assessments will be performed by individual researchers at Biogen, at the MS PATHS academic institutions, and/or by their collaborators.

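### Table 1 footnotes 7 and 8 cap biomarker draws at one per 10 months without exempting Unscheduled Visits, contradicting the rest of the protocol

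*Protocol*

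**What the plan says.** **The cap.** Footnotes 7 and 8 to Table 1 (Protocol Section 4) each state that "blood collection for future biomarker assessments will typically occur during routine clinical visits but not more frequently than every 10 months". They are attached to the row "Blood Collection for RNA, Serum, and Whole Blood Biomarker Samples", which has an X under Baseline, Follow-Up and Unscheduled Visits.

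**The 10-month rule elsewhere.** Section 7.2.2 and footnote 2 apply it to the annual Follow-Up Visit, which should "not occur more frequently than 10 months since the last Baseline or Follow-Up Visit". Footnote 3, the closing line of Section 7.2.3 and the synopsis add one rule: "After an Unscheduled Visit, the next annual Follow-Up Visit should occur no sooner than 10 months later". Each of these sets the earliest date of the next annual visit. None limits when an Unscheduled Visit may take place.

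**Unscheduled Visits.** Section 7.2.3 opens: "Unscheduled Visits will be permitted for the following events as determined by the Investigator". It lists relapse, MRI activity, a new MS PATHS MRI, a DMT switch and a DMT switch follow-up. Each has a window relative to its own event, and none has a minimum gap from the previous draw.

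**Draws.** Sections 11.1.1 and 11.1.2 provide for the biomarker draw at every visit. The sample requisition form in Section 11.2 has a field for the reason for an Unscheduled Visit.

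**The concern.** What footnotes 7 and 8 limit is blood collection itself, not the annual visit. A relapse visit four months after Baseline is permitted by Section 7.2.3 and calls for a draw under Section 11.1, but footnote 7 or 8 forbids that draw.

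Section 11 opens with "See Section 4 for the timing of all study procedures", so the footnotes are part of the timing text that sites are told to use. About 10 sites in the United States and Europe are planned. A site that follows the footnote omits relapse, MRI and DMT-switch samples. A site that follows Section 7.2.3 takes them and may have them recorded as deviations. The event samples in the shared biobank would then differ by site for a reason unrelated to the patients, and a sample not drawn at the event cannot be recovered later.

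Section 14.1 names pharmacodynamic responses and treatment-related changes among the intended uses, and the DMT-switch pair bears directly on these.

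**Working it through.** The protocol gives no sample size or power figure to reproduce (Section 14.2 says none was calculated). The check compares intervals.

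**Inputs**
- Minimum interval between biomarker draws: 10 months (Table 1 footnotes 7 and 8).
- DMT switch visit: "An Unscheduled Visit for a DMT switch should occur within 30 days of the first administration of the new therapy" (Section 7.2.3, item 4).
- Follow-up visit: "An Unscheduled Visit for a DMT switch follow-up should occur within 90-240 days after the first administration of the new DMT" (Section 7.2.3, item 5).

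**Step 1: 10 months in days.** 10 × 365.25 / 12 = 304.4, or about 304 days. Counted on the calendar, it is 303 to 306 days depending on the start date.

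**Step 2: gap between the two DMT draws.**
- Smallest gap: 90 − 30 = 60 days.
- Largest gap, switch draw on or after the first dose: 240 − 0 = 240 days.
- Largest gap, if the 30-day window also allows a draw before the first dose: 240 + 30 = 270 days.

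**Step 3: comparison with the cap.**

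| Reading of the switch window | Largest gap (days) | Shortfall against 304 days | Range by calendar (303–306) |
|---|---|---|---|
| On or after first dose | 240 | 304 − 240 = 64 | 63–66 |
| Before or after first dose | 270 | 304 − 270 = 34 | 33–36 |

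The shortfall is positive in every case. A patient who attends both visits in window and is bled at both always breaches the literal cap.

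**Step 4: other event draws.** Assume annual draws exactly 12 months apart. On the literal reading the first 10 months after each draw are closed to event sampling: 10 / 12 = 83% of the interval.

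**Step 5: blood volume.** Baseline, switch and follow-up draws can all fall within 10 months. For adults that is 3 × 28 = 84 mL of biomarker blood, against 28 mL under the literal cap. For ages 8 to 17 it is 3 × 13.5 = 40.5 mL against 13.5 mL. The two rules therefore also imply different blood volumes for the same patient.

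**The case against.** The strongest reply is that the intent is clear from the same table. The row carries an X for Unscheduled Visits, footnote 3 allows those visits, and footnote 6 has the form record their reason. The literal reading would also leave an Unscheduled Visit inside 10 months with almost nothing to do: the only rows marked X for it are the requisition form and the biomarker draw, and Section 11.2 has the form completed when blood is collected. The footnote sentence mentions routine clinical visits and resembles the annual rule in Section 7.2.2, so it can be read as covering only the routine annual draw. A detailed protocol review takes place at site initiation, and the Laboratory Manual, not available here, holds further procedures. Unscheduled Visits are also at the investigator's discretion, so event samples will vary by site in any case.

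Much of this stands. The intent can be recovered, nothing shows that a site has applied the cap literally, and the 83% and the 34-day shortfall measure the conflict in the text, not an expected loss of samples.

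It does not remove the contradiction. In the footnotes, the word for typical timing qualifies the link to routine visits, not the limit that follows. Footnote 2 and Section 7.2.2 show how the narrower rule is written, and footnotes 7 and 8 lack that restriction. Nor does every other passage point one way: Section 7.2 describes the sub-study as made up of Baseline and Follow-Up Visits and omits Unscheduled ones. Investigator discretion is no reason to add a second, unintended source of site variation.

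**Conclusion.** The point holds. Footnotes 7 and 8 are wrong as written: they contradict the X on their own row, Section 7.2.3 and Sections 11.1.1 and 11.1.2. This is an internal inconsistency, almost certainly a wording slip, and not a disputed design decision.

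The conflict is certain for the DMT-switch pair, where even the widest gap of 270 days is about 34 days short of 10 months. For other event draws it arises whenever the event falls within 10 months of the previous draw. That part assumes annual draws 12 months apart and a site that applies the footnote as written; how many sites would do so cannot be judged from the protocol.

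The harm is limited to which event samples reach the biobank. No sample size, power figure or planned estimate depends on the footnotes. The correction should be made, but it does not call the design into question.

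**What to change.** Amend footnotes 7 and 8, keeping their tube and volume details, so that the timing text reads for example:

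> Biomarker blood is usually drawn at routine clinical visits. An annual Follow-Up draw should take place no sooner than 10 months after the last Baseline, Follow-Up or Unscheduled Visit. Draws at Unscheduled Visits under Section 7.2.3 are exempt from this minimum interval.

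This keeps the existing rules in Section 7.2.2, footnote 3 and Section 7.2.3, including the 10-month wait for the next Follow-Up Visit after an Unscheduled Visit. The 60-to-240-day DMT pair (up to 270 days) becomes permissible, and the footnotes agree with Table 1 and Section 11.1.

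The cost is the wording of two footnotes in one amendment, with no new procedure, visit or data field.

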## 5. INTRODUCTION

### 5.1. Overview of Multiple Sclerosis

Multiple sclerosis (MS) is a chronic inflammatory demyelinating disease of the central nervous system (CNS) that affects approximately 400,000 persons in North America and 365,000 persons in Europe. It is predominantly a disease of young adults, primarily women, with disease onset typically occurring between the ages of 20 and 40 years. MS is the most common form of inflammatory demyelinating CNS disease and the most common cause of nontraumatic neurological disability in young adults. Disease progression and advancing disability are common in patients with MS who are followed for several years.

MS is a heterogeneous disease that can affect a wide range of functional systems, resulting in symptoms that vary from one patient to another. More importantly, the MS spectrum can vary in severity from an active and aggressive disease course from the onset to a mild disease with infrequent relapses [Confavreux 2000]. While early management of MS disease activity is recognized as important for preventing relapses and long-term disability, early intervention in and of itself does not necessarily assure an optimal outcome given the heterogeneous responses to treatment that have been observed.

Information relating to the pathophysiological basis of MS has the potential to further enhance our understanding of the disease and to make possible a personalized patient medicine approach. Genetic, genomic, proteomic, and other existing biomarker data indicate that there are multiple genotypes and clinical phenotypes underlying the disease collectively referred to as MS [Achiron 2012; De Jager 2011; Hecker 2011; Martinelli-Boneschi 2012; Ottoboni 2012; Vecchio 2011]. It is hypothesized that patients with different disease phenotypes will not only exhibit different disease courses but also will respond differently to a given treatment, leading to inter-individual differences in clinical response. It is postulated that clinical, radiologic, and/or molecular features of a given patient may eventually enable an individualized prognosis regarding risk for subsequent disease worsening as well as inform treatment decisions.

### 5.2. Overview of Learning Health Systems

The Institute of Medicine (IOM) issued a report in 2013 describing the concept of a Learning Health System (LHS) that capitalizes on the existing patient data that flow through the health care system to advance clinical knowledge with every patient visit [IOM 2013]. The report outlined the necessity to evolve such a system to achieve greater value in health care for all stakeholders. The American health care system has been struggling to achieve a level of consistent quality, efficiency, and safety across the nation that, if achieved, could save many lives. Paradoxes in the health care system have held back this advancement of care and value for a multitude of reasons. Although the IOM report is focused on the American health system, many health systems around the globe face similar challenges. First, the coexistence of over-treatment and under-treatment can leave patients with either unnecessary and expensive care or a lack of adequate care due to an absence of standard evidence-based protocols. Second,

CONFIDENTIAL

The information contained herein may not be used, disclosed, or published without the written consent of  
Biogen MA Inc.

patients' health challenges and the health care system are becoming increasingly complex. As the population grows older, patients are developing more comorbid diseases, but treatment guidelines have not adapted to handle this challenge. Third, the American health system's understanding of diseases is expanding, but with the expansion of medical knowledge comes increasingly complex disease sub-types. Finally, new drugs and devices are being increasingly introduced, but evidence to support identifying the most effective drugs for various disease sub-types continues to lag behind. To move health care forward and establish evidence-based guidelines, an LHS needs to be formed.

The crux of an LHS is aggregation of data from routine clinical practice that can be subsequently used to generate knowledge and insights to improve patient care. The IOM lays out 4 important steps to achieving this LHS. First is generating and using real-time knowledge to improve outcomes. The second key step to achieving an LHS is creating a "culture of care" that supports the vision of continuous improvement with each patient visit. Physicians face pressures from time, chaotic environments, inefficient workflows, administrative burdens, and uncoordinated systems that can distract initiatives that focus on improving care. Having strong leadership and governance that incentivize systematic problem solving, experimentation, and learning from past experiences is essential to minimizing these distractions and focusing on advancement of clinical knowledge. The third step is engaging families, patients, and communities to improve communication and create a truly patient-centered care system. Engaging patients in their own care decisions allows them to give a personal perspective on the suitability of treatments, which can ultimately result in more effective care for the patient. Additionally, involving the patient by collecting self-reported outcomes can help engage them and expand the knowledge base without adding burden to the clinician. Finally, the fourth step is achieving and then rewarding high value care through payment models that focus on value instead of individual services and products. Transparency in payment will help patients choose appropriate providers, which will, in turn, encourage providers and organizations to achieve higher value. These 4 steps can help create a true LHS, where clinicians, researchers, and, ultimately, patients will benefit from a focus on learning through data.

The MS population would especially benefit from such a system, as treatment protocols for MS are less standardized in comparison to other disease states, and few evidence-based treatment guidelines exist to indicate which patients will respond best to the numerous therapies on the market.

### **5.3. Overview of Multiple Sclerosis Partners Advancing Technology and Health Solutions**

The parent study is Multiple Sclerosis Partners Advancing Technology and Health Solutions (MS PATHS), which is a demonstration project of an LHS in MS (the demonstration project is henceforth referred to as Study 888MS001). Study 888MS001 and its sub-studies are being launched by Biogen in collaboration with select health care institutions.

This demonstration project will specifically focus on leveraging technology to generate and aggregate de-identified data from routine care visits across multiple institutions. The goal is to

CONFIDENTIAL

The information contained herein may not be used, disclosed, or published without the written consent of  
Biogen MA Inc.

ultimately improve outcomes in MS by enabling real-world, broad-scale MS phenotyping that is needed to better understand MS, predict therapeutic responses, and develop meaningful approaches to personalized medicine.

MS PATHS aims to engage all providers and nearly all patients with a confirmed diagnosis of clinically isolated syndrome or MS (henceforth referred to as MS patients) in an MS center to standardize, quantify, and maximize data collected as part of routine care. The demonstration project plans to leverage existing and developing technology with the goal to reduce the data collection burden on health care providers and staff (e.g., Multiple Sclerosis Performance Test device). In addition, the demonstration project will include separately consented sub-studies to collect data outside of routine care. This infrastructure aims to enable researchers to access a large set of longitudinal patient data to advance the knowledge of MS disease progression and patients' response to therapies.

